#### Economic evaluation

A cost-effectiveness analysis will be conducted. The primary (quality of care) and secondary (e.g., Quality-Adjusted Life Years, QALYs) outcome measures will be used as indicators of effectiveness [58]. The QALYs will be calculated using health utility scores estimated by the Korean EQ-5D-5 L tariff [32]. In the analysis, incremental cost-effectiveness ratio (ICER)—defined as the difference in costs between the SPEC and usual care divided by the difference in the effect of the two types of care—will be assessed [59]. If the SPEC program is more costly and also more effective, we will calculate the incremental costs and effects. If the SPEC program is as effective as usual care, we will do the economic evaluation based on incremental costs only [60].

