### Outcomes

Quality of care is the primary outcome, and several secondary outcomes including quality of life will be measured. We have also included process measures and staff-/organization-related measures as complementary. All outcomes and their measurement plans are summarized in Table 2, except the process evaluation measures, which are in Table 3.

**Table 2 Tab2:** Overview of the outcome variables, measures, and observation points

Variable	Data Source/Instrument	Measurement Points	Unit of Analysis
Primary Outcomes			
Quality of Care	interRAI LTCF quality measures (composite score)	T0 (baseline), T1, T2, T3	Resident
Secondary Outcomes: Patient-Related			
Quality of Care	interRAI LTCF quality measures (individual score)	T0 (baseline), T1, T2, T3	Resident
Care Needs	Number of triggered clinical action points of interRAI LTCF	T0 (baseline), T1, T2, T3	Resident
Functional Health	Bathel index; Mini-Mental Status Examination; Patient Health Questionnaire	T0 (baseline), T1, T2, T3	Resident
Quality of Life	EuroQol(EQ)-5; interRAI HRQoL; interRAI self-reported QoL (SQoL)	T0 (baseline), T1, T2, T3; T1 & T3 (SQoL)	Resident
Patient Satisfaction	Client Satisfaction Questionnaire	T1 & T3	Resident
Health Care Utilization	Hospital admissions; emergency department visits	Every three months	Resident
Costs	Questionnaire on the cost; direct and indirect costs	Every three months	Resident
Other Outcomes: Care Staff/Organization-Related			
Empowerment	Psychological Empowerment Instrument	T1 & T3	Nursing Home
Communication Satisfaction	Communication Satisfaction Questionnaire	T1 & T3	Nursing Home
Organizational Commitment	Organizational Commitment Questionnaire	T1 & T3	Nursing Home
Job Satisfaction	Job Satisfaction Scale	T1 & T3	Nursing Home
Technology/Innovation Acceptance	Modified Technology Acceptance Model Questionnaire	T1 + 1 month & T3	Nursing Home

**Table 3 Tab3:** Process evaluation on intervention and implementation strategies

Topic	Data Source/Analysis	Measurement Points	Unit of Analysis
Recruitment of cluster	[Qualitative analysis] - Measurement from documentation of recruitment & allocation process by research team	During recruitment of clusters	Nursing home

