*Patient satisfaction* will be measured with the K-CSQ (Korean Client Satisfaction Questionnaire) [34]. The original CSQ developed by Larsen et al. [35] has six different forms, and CSQ-8, consisting of 8 items, is most widely used in consumer or client satisfaction studies. The K-CSQ by Kim et al. [34] is a translated and modified version of CSQ-8 to measure the satisfaction of nursing home residents in Korea; good psychometric properties have been reported.

As for *health care utilization*, costs will be collected from a societal perspective and consist of medical costs and intervention costs. Medical costs will be calculated by multiplying the healthcare utilization and unit costs. Other healthcare utilization data includes the number of physician visits, length of stay, service use in the facilities, and time consumption. Nationally representative data—such as the National Health Insurance database [36] and Korea Health Panel Survey data [37]—will be used to calculate the unit costs. Intervention costs that occur while operating the SPEC program will also be calculated. Productivity costs are to be excluded, taking into account the old age and frail health status of the residents.

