### Data analysis plan

#### Effect evaluation

Baseline differences between clusters during the first control period will be tested using chi-square tests and ANOVA. The primary analysis will be the evaluation of the interventional effect of the SPEC program in nursing homes. The intervention effect on the primary outcome and secondary outcomes described above will be estimated using a multilevel regression analysis to account for the clustered structure [54]. We will use a generalized linear mixed effects model [54], which allows inclusion of both fixed (intervention, time) and random factors. In particular, two random effects will be introduced, one at the cluster (nursing home) level and the other at the individual (resident) level. The test statistic to assess any significant benefit of the intervention will be calculated. We will use two-sided p-values with alpha = 0.05 for level of significance. Compliance issues will be handled as in Jo et al. [55].

A secondary analysis will be conducted to adjust for the potential confounding effects of pre-randomization variables. The same generalized linear mixed effects model will be used to model the primary and secondary outcomes, adjusted for socio-demographic variables including age, sex, physical status, and cognitive status as well as an intervention indicator and time. We will also investigate the effect of the duration of the intervention by adding an interaction term between time and intervention as a fixed effect. Furthermore, subgroup analysis will be used to explore the subgroup-specific effects of the intervention on outcomes. The interaction effects of the intervention with dependency in activities of daily living and cognitive impairment will also be explored. When a statistically significant difference is found, the study population will be split to examine the results for each subgroup separately. We will also conduct an analysis of the intervention effects on facility-level pre-post measurements using a t-test. In addition, we will develop models to evaluate the impact of the program on resident-level outcomes while adjusting for facility-level factors. A *p*-value of 0.05 or less will be considered to be significant.

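### The economic evaluation drops effects if SPEC proves equally effective, a finding the planned tests cannot establish; the cost perspective and Table 2 also disagree

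*Protocol article*

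**What the plan says.** The Economic evaluation section plans a cost-effectiveness analysis with an incremental cost-effectiveness ratio. It names two kinds of effect measure: "The primary (quality of care) and secondary (e.g., Quality-Adjusted Life Years, QALYs) outcome measures will be used as indicators of effectiveness". Two conditional rules follow. The first is "If the SPEC program is more costly and also more effective, we will calculate the incremental costs and effects". The second is "If the SPEC program is as effective as usual care, we will do the economic evaluation based on incremental costs only". Neither says how equal effectiveness is to be judged, or on which measure.

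The only inferential rule for effects is in the Effect evaluation section: "We will use two-sided p-values with alpha = 0.05 for level of significance". It applies to a generalized linear mixed model with fixed intervention and time effects and random home and resident effects. No equivalence margin appears in the article.

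On costs, the Secondary outcome measures section states that "costs will be collected from a societal perspective and consist of medical costs and intervention costs", and then: "Productivity costs are to be excluded, taking into account the old age and frail health status of the residents". The cost row of Table 2 reads: "Questionnaire on the cost; direct and indirect costs".

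**The concern.** The cost-only rule needs a conclusion, equal effectiveness, that none of the planned analyses can deliver. A two-sided difference test that fails to reject leaves open both no effect and a worthwhile effect.

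Once the branch is entered, the effect estimate leaves the economic evaluation, together with its uncertainty and its covariance with cost. That loss occurs however the branch is triggered, so a definition of equal effectiveness in a fuller document would remove the vagueness but not the loss.

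The rule can also point both ways. If quality of care improved while QALYs showed no clear difference, each branch would apply to one measure, and the text does not say which prevails. The form of the evaluation could then be settled after the results are known.

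On costs, the article gives two descriptions of what is counted. A reader of the eventual ratio could not tell which costs it contains or whether the perspective label fits them.

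**Working it through.** **The plan's own figures.** The Economic evaluation section states no number. The nearest are in Sample size & recruitment.

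- Beds: 45 / (0.80 × 0.85) = 66.2, rounded up to 67. This reproduces.
- Cluster size with the outcome measured separately at each time: 33. This reproduces with five sequences of two homes, four measurements per home (two control, two intervention), fixed period effects, intracluster correlation 0.01, within-resident correlation 0.25 and variance 0.115 × 0.885.
- Cluster size 45: this cannot be checked, because the article does not give the correlation matrix for indicators defined as differences between successive times. The steps below use only the stated power, so they do not depend on it.

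**Inputs for the check** (Sample size & recruitment): proportions 0.115 and 0.182, power 80%, two-sided alpha 0.05. The planned effect is 0.182 − 0.115 = 0.067.

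**Step 1, implied precision.** SE = 0.067 / (1.960 + 0.842) = 0.0239. The 95% interval half-width is 1.960 × 0.0239 = 0.047, and 0.047 / 0.067 = 70% of the planned effect.

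**Step 2, what a non-significant result leaves open.** An estimate of exactly zero has an interval of about −0.047 to +0.047. An estimate just short of significance, 0.047, has an interval reaching 2 × 0.047 = 0.094, which is above the full planned effect.

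**Step 3, how often the branch would be entered, if equal effectiveness is read as non-significance on the primary outcome.** Probability = 1 − [Φ(δ/SE − 1.960) + Φ(−δ/SE − 1.960)], with SE held at 0.0239.

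| True effect δ | Share of planned effect | Non-significant |
|---|---|---|
| 0.067 | full | 20% |
| 0.050 | three quarters | 44% |
| 0.0335 | half | 71% |

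The article states no power for QALYs, so the same calculation cannot be made for that measure.

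**Step 4, cost descriptions side by side.**

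| Place | What is counted |
|---|---|
| Secondary outcome measures | Labelled societal; two categories, medical and intervention costs; productivity costs excluded with a reason |
| Table 2, cost row | Direct and indirect costs |

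The text names no indirect cost category. It lists time consumption among utilization data, but does not say whose time it is or that it will be costed. Family members take part in care planning (Components of SPEC; Procedure), yet no family time cost is named.

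**The case against.** The strongest reply is that the article nowhere ties equal effectiveness to a p-value. A reader might infer that a non-significant effect will be treated as zero. The article does not say so, and the rule carries a citation that cannot be consulted here. A threshold may sit in a fuller protocol or analysis plan, and its absence from a condensed article would not by itself be a fault. That stands, so the percentages in Step 3 are conditional on one reading. It does not rescue the rule, which is stated, rests on a finding that a difference test cannot supply, and removes the effect from the evaluation however that finding is reached.

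A reader might also infer that an effective programme could be rejected on cost alone. The article contains no adopt-or-reject rule, the effect is still estimated under Effect evaluation, and Ethics and dissemination commits to publishing the results whatever they show.

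A third inference would be that QALYs are distorted because the control period lasts three months and the intervention about six. Nothing says that raw totals over unequal windows would be compared, and secondary outcomes are modelled with time terms.

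On perspective, a reader might conclude that the societal label is simply wrong. The productivity exclusion is disclosed and justified by the residents' age and frailty, and for this population it does not by itself defeat the label. Table 2 also points to a wider cost set than the text. The documents therefore show a mismatch; they do not show which side is right.

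**Conclusion.** The point holds in two parts.

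- **Cost-only rule.** The form of the economic evaluation depends on an undefined finding of equal effectiveness, which the planned tests cannot establish, on one of two measures without saying which. Read as non-significance on the primary outcome, the branch would be entered in about 20% of trials at the full planned effect and about 71% at half of it. These figures assume that the stated 80% power is achieved, that the estimate is approximately normal, and that its standard error does not change with the true effect.
- **Cost definition.** The text and Table 2 disagree on what is counted under a societal label. The article allows no estimate of how far this would move the ratio.

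Both parts concern a secondary evaluation, and the primary analysis is unaffected. Correction is worthwhile because the remedy is cheap and, according to Trial status, analysis had not begun.

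**What to change.** 1. Delete the cost-only sentence. Whatever the effect test shows, estimate incremental cost and incremental effect jointly for both quality of care and QALYs. This also removes the question of which measure governs.
2. Work per three-month interval, with the same time terms and the same home and resident random effects as the effect model. Table 2 already schedules costs every three months and the EQ-5D at T0 to T3.
3. Report joint uncertainty, for example as net benefit over a range of willingness-to-pay values, by a method that respects ten homes in five sequences. A plain bootstrap of homes is fragile here. Drawing ten homes with replacement misses a given sequence with probability 0.8^10 = 0.11, and at least one of the five with probability 5(0.8^10) − 10(0.6^10) + 10(0.4^10) − 5(0.2^10) = 0.48. A joint mixed model for cost and effect is one alternative.
4. Reconcile Secondary outcome measures with Table 2. List the cost items actually collected, say whether any indirect cost (including family time) is counted, and make the perspective label match.

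The cost is analysis-plan wording and some programming. Items 1 to 3 need no new data. Item 4 is wording, plus the costing of any indirect items already collected.

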#### Process analysis

The goal of process evaluation of this study is to understand the context, integrated process, and results of the intended intervention program, and also can give insights into applying the same intervention to a different setting in the future [49]. Guided by the framework for designing process evaluation for cluster-randomized trials of a complex intervention [61], we aim to explain the potential differences between the expected and real outcomes, and provide insights on the facilitating and inhibiting contextual factors in program implementation as well as the intervention process, recruitment strategies, etc. [62]. Quantitative data will be analyzed using descriptive statistics, and qualitative data will be analyzed using content analysis, document analysis, etc.

### Ethics and dissemination

This study was approved by the institutional review board (IRB) of human subjects where the first author is affiliated (SNU IRB 1410/002-018). No critical protocol modifications have been made; and if they are, such changes will be communicated to all relevant parties, including the IRB, trial participants, the trial registry, journals, etc. In order to make sure the participation of older residents is voluntary, following the recommendation of the IRB, an adult attendant with no conflict of interest attends the consent-attainment process and co-signs the consent form to indicate the consent has been properly acquired. A password-protected electronic file including personal information, separate from the trial dataset, is saved in a password-protected computer in a locked room. None of the investigators or participating sites have financial or competing interests. Only the PI and those with the permission of the PI will have access to the final trial dataset. We plan to present the trial results in academic conferences, publish articles in peer-reviewed journals, and report to the trial registry when the analyses finish, regardless of the magnitude or direction of the effect. Authorship eligibility will follow the ICMJE guidelines, and we do not plan to hire professional writers.

### Trial status

The study has been rolled out to all ten nursing homes, and data collection is ongoing at the submission of this manuscript. Data analysis has not yet started.

## Discussion

As far as we know, this is the first registered trial to evaluate a CCM-based, ICT-enhanced geriatric care model for older people with multi-comorbidities in South Korea. We have developed and are evaluating the multifaceted SPEC intervention, implementing a multidisciplinary care management program. The program promotes person-centered care for older people through individualized CP based on CGA, and incorporates the preferences and choices of older residents and their families. We expect the SPEC model will support the nursing home staff to organize and deliver care in a more resident-centered way, which would primarily improve quality of care, which in turn would contribute to the health and well-being (quality of life) of older residents. The intervention will be tailored to each participating nursing home’s existing administrative routine, level of advancement in care planning, and management system, as well as to the needs and preferences of the identified older adults and/or their family members.

As for study design, this SPEC study adopted a stepped-wedge cluster randomized trial (SWCRT) design [11, 63, 64], which is appropriate for this study in several ways. First, the SWCRT design provides an opportunity for all participating nursing homes to get the intervention at different time-points during the intervention period. This was a critical point in the recruitment of the participating homes, which are resource-limited and busy in their day-to-day practice; they all wanted to get the intervention as a condition for participation. Second, the design is suitable for the research team, which, with its limited budget and manpower, would not be able to roll out the intervention to all ten nursing homes at the same time while ensuring the quality of implementation. Third, the study design allows an estimation of the intervention effects using both a between- and within-cluster comparison.

There are several anticipated challenges. The constraints in financial and human resources may decrease the fidelity of participating nursing homes to the implementation of the SPEC program. Along with these resource limitations, preparations for an anticipated mandatory quality inspection by the government [12], the top priority of nursing home administrators, also could weaken nursing homes’ commitment to the SPEC program. Other potential challenges include difficulty in engaging nursing home staff to learn and practice new knowledge and skills for conducting CGAs and CP along with using the new ICT system, as many nursing homes still rely on paper-based charting systems. Getting cooperation from frail older residents for data collection is another anticipated challenge. Along with several strategies described above to improve study fidelity, the study team will provide tailored guidance, support, and encouragement for each participating home, as the barriers and facilitators each home faces may differ. One possible strategy for retention of older residents is to decrease the burden of being interviewed for data collection by adjusting the data collection schedule and time. Similarly, the research team will adjust the time and place for education and evaluation at each home as much as possible within the given data collection schedules.

## Abbreviations

CC: Care coordination
CCM: Chronic care model
CGA: Comprehensive geriatric assessment
CP: Individualized need-based care planning
DMC: Data monitoring committee
ICC: Interdisciplinary case conference
ICT: Information and communication technology
LTC: Long-term care
LTCF: InterRAI Long-term care facilities
LTCI: Long-term care insurance
QALYs: Quality-adjusted life years
QI: Quality indicator
SPEC: Systems for person-centered elder care
SWCRT: Stepped-wedge cluster randomized trial
